#### Track record document

A document is being created and maintained by the WHO Regional Office for Europe to record meeting minutes of management committee meetings (with strategic managers/partners) and meetings with partners in Denmark and Romania. This document will serve as a resource to document our implementation processes, how decisions were made throughout and to explore key learning points from the project, as well as to assess fidelity of delivery.

#### Screening and attendance logs

Logs will be created and maintained by project managers/coordinators to document the number of people who were screened and how many of these individuals went on to participate in the intervention. A record will also be kept of intervention attendance by the singing leader, including whether any participants drop out throughout the 10-week programme. This will help us to assess the reach of the project (ie, whether the intended audiences came into contact with the intervention and how).

#### Active ingredients worksheet

To aid the process of tracking and understanding any adaptations made to the intervention throughout the process of implementation, the INNATE framework will be used.^37^ This framework puts forward a comprehensive mapping of 139 active ingredients (the components of an intervention that may prompt the mechanisms of action underlying potential health outcomes) which can be used to describe, in depth, the key aspects of an intervention that may be important to health. The framework will be used to identify, and reflect on, intervention active ingredients at the planning stage of the intervention (ie, the week before the classes are implemented in each country) and then again after the intervention is complete (ie, after week 10). This tool will therefore support with assessing fidelity of delivery through documenting adaptations to the intervention that occur organically, as well as provide a document that could be used to support with replication of the intervention into other countries in the future.

### Perceived impact of intervention methods

#### Survey

Intervention participants will be invited to complete a short (5-minute) quantitative survey at three time points throughout study participation (weeks 1, 6 and 10). Participants will be contacted via email with the surveys and followed up with email reminders to improve adherence. These surveys have been kept purposely short to try and keep the process simple and easy for participants to engage in (see table 2).

**Table 2 T2:** Quantitative measures to evaluate the perceived impact of the intervention on mental health and well-being for singing participants

Outcome	Type	Measure	When
Postpartum depression	Quantitative	Edinburgh Postnatal Depression Scale	Weeks 1, 6 and 10
Social support	Quantitative	Multidimensional Scale of Perceived Social Support	Weeks 1, 6 and 10
Well-being	Quantitative	The World Health Organization Five Well-Being Index	Weeks 1, 6 and 10

#### Focus group

All intervention participants will be invited to join one focus group at the end of the 10-week programme (one focus group per singing group). The groups will explore subjective experiences of the weekly sessions such as in relation to what participants enjoyed/did not enjoy, any challenges that occurred, and the perceived impact of the classes on PPD symptoms, social relationships, and identity. The focus group is anticipated to last 60–90 min. Given the potential sensitive nature of discussing maternal mental health, focus group facilitators will receive specific training delivered by UCL on how to conduct these sessions in a sensitive way.

#### Optional reflective journal entry

Study participants will be given the option to complete a journal entry at the end of the singing programme to reflect on anything they feel they have been unable to share at other data collection points.

In addition to the above qualitative and quantitative data, we will also collect sociodemographic data (location, age, ethnicity, educational attainment).

See figure 1 for a flow diagram of all of our data collection time points and measures.

**Figure 1 F1:**
[figure not shown]
Study flow chart. Diagram showing data collection time points and measures collected for singing intervention participants and the implementation team. EPDS, Edinburgh Postnatal Depression Scale; MSPSS, Multidimensional Scale of Perceived Social Support; PIS, participant information sheet; WHO-5, WHO Five Well-Being Index.

### Data analyses

#### Quantitative

Data will be analysed using Stata and/or MASPSS. Descriptive statistics will be used to analyse the implementation short survey (AIM, IAM, FIM), and repeated measures analysis of variance will be used to explore changes to mental health and well-being across time for our singing intervention participants (within-subject changes). Analysis of covariance will additionally explore whether these changes are moderated by participants’ sociodemographic backgrounds.

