### Participants

Data will be collected from different project stakeholders (coined the ‘implementation team’ for this protocol) to examine how the intervention is delivered. This will include four groups:

Strategic managers/partners (n=7) involved in planning and overseeing the intervention delivery and success (eg, members of the management committee from Region Midtjylland, Cluj Culture Centre and Den Creative Skole who meet regularly with the WHO Regional Office for Europe and UCL for planning meetings).Project managers/partners (n=7) involved in coordinating and managing the on-the-ground delivery of the intervention (eg, project coordinators working at Cluj Culture Centre and Region Midtjylland).Referrers (n≈8) (such as health nurses in Denmark or other health/non-governmental organisation (NGO) professionals in Romania) who refer participants to be included in the intervention.Singing leaders (n=3) who will lead the practical and creative delivery of the intervention. One in Denmark, two in Romania.

All managers/partners and singing leaders will need to speak English sufficiently enough to read the information sheet and give informed consent (see online supplemental files 1 and 2). Referrers and singing leaders will be able to participate in Danish or Romanian. All stakeholders must be aged over 18 years to participate. Project managers/partners from across both countries will engage in regular biweekly online meetings with the strategic management team as a form of supervision, ensuring ongoing reflection on ethical practice (in relation to both delivery of the intervention to participants and ensuring staff well-being) and fidelity of delivery.

10.1136/bmjopen-2022-063420.supp1Supplementary data

10.1136/bmjopen-2022-063420.supp2Supplementary data

Data will also be collected from our singing intervention participants to explore the perceived impact of the singing classes. Based on class sizes that have been successful in the context of the United Kingdom,^19^ the aim is to include two groups of 8–12 participants in each country, a total of 32–48 participants in total across both Denmark and Romania. Of note, we did not calculate our sample size in view of determining statistical power, instead focusing on how to feasibly implement the intervention and explore its perceived impact. The inclusion criteria are women who:

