Score ≥10 on the Edinburgh Postnatal Depression Scale (collected upon screening).Are up to 40 weeks post-birth with an infant aged 0–9 months.Are aged 18 years or over.Have the capacity to give informed consent.

Potential singing intervention participants who cannot speak Danish, Romanian, Hungarian or English to a level that is sufficient to read and understand the information sheets and consent forms for the study (either through reading or being read to) will be excluded, as will those under the age of 18 years or those who have infants not aged 0–9 months (see participant consent forms in online supplemental files 3 and 4). Participants can still join if they are receiving other treatments.

10.1136/bmjopen-2022-063420.supp3Supplementary data

10.1136/bmjopen-2022-063420.supp4Supplementary data

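### Repeated measures ANOVA in its standard form discards every mother with a missing survey; a mixed model on all available surveys would waste less of a small sample and be less open to drop-out bias

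*Protocol article*

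**What the plan says.** The Quantitative part of Data analyses fixes the method: "repeated measures analysis of variance will be used to explore changes to mental health and well-being across time for our singing intervention participants". The abstract repeats it. On software it says "Data will be analysed using Stata and/or MASPSS"; I read the second name as SPSS, which is an assumption. Analysis of covariance is added to look at moderation by sociodemographic background. The article states no rule for incomplete surveys and names no term for singing group.

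Table 2 puts all three measures at weeks 1, 6 and 10. On collection, the Survey section says: "Participants will be contacted via email with the surveys and followed up with email reminders to improve adherence". Drop-out is foreseen. The attendance record is kept "including whether any participants drop out throughout the 10-week programme", and the section on one-to-one interviews offers an interview to women who leave.

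On size, the Participants section says "the aim is to include two groups of 8–12 participants in each country", giving "a total of 32–48 participants in total across both Denmark and Romania", and adds that "we did not calculate our sample size in view of determining statistical power". Impact on mental health is the secondary aim; feasibility is the primary one.

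**The concern.** The named method fits poorly with the data that the same document expects. Within-subject ANOVA in its usual wide-format form needs a full row of three surveys per mother. A mother who answers at weeks 1 and 6 but not at week 10 contributes nothing, not even to the change from week 1 to week 6.

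Two things are at stake. The first is information: with at most 48 mothers, each discarded row matters. The second is bias: if the mothers who stay in the analysis differ in their earlier scores from those who fall out, the reported change describes a selected subset.

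A related, smaller point is that mothers are taught in four groups. If the change itself differs between groups, an interval that treats all mothers as independent is too narrow for any statement about groups other than these four.

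**Working it through.** **Stated sample size.** 2 countries × 2 groups × 8 = 32 and 2 × 2 × 12 = 48. The plan's 32–48 reproduces. It gives no power, SD, drop-out rate or intraclass correlation (ICC), so every input below is an assumption.

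**Mothers lost.** Assume 0–10% missing at week 1, 10–20% at week 6 and 20–30% at week 10.
- Misses independent between waves: the complete share is the product of the response rates. Low: 0.9 × 0.8 × 0.7 = 0.504. High: 1.0 × 0.9 × 0.8 = 0.72. That is 32 × 0.504 ≈ 16 to 48 × 0.72 ≈ 35 mothers.
- Nested loss (once out, always out): the complete share is the week 10 response rate, 0.70–0.80. That is 32 × 0.70 ≈ 22 to 48 × 0.80 ≈ 38 mothers.

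The loss is therefore 28–50% or 20–30% of mothers, or 20–50% overall. Drop-out is mostly nested and skipped emails are not, so the truth probably lies between the two patterns.

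**Bias.** Simulated EPDS at three waves with SD 5, means 14, 12 and 10 (true change −4.0), wave correlations 0.5–0.6 (0.4–0.6 in the third row) and only week 10 missing. The mixed-model column is the likelihood-type estimate from all observed data.

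| Loss at week 10 depends on | Missing | Complete cases | Mixed model |
|---|---|---|---|
| nothing (completely random) | 15 / 25 / 40% | −4.0 / −4.0 / −4.0 | −4.0 / −4.0 / −4.0 |
| week 1 score | 15 / 25 / 40% | −3.7 / −3.5 / −3.2 | −4.0 / −4.0 / −4.0 |
| poor change from week 1 to 6 | 28% | −4.3 to −5.1 | about −4.0 |
| the unseen week 10 score | 15 / 25 / 40% | −4.3 / −4.5 / −4.9 | −4.4 / −4.7 / −5.1 |

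The range in the third row reflects how strongly poor change drives loss. Complete cases can understate the fall (by 0.3–0.8 points when loss follows the week 1 score), overstate it (by 0.3–1.1 points when loss follows poor early change) or be right. The mixed model is right in the first three rows and wrong in the last, where it does slightly worse than complete cases.

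**Groups.** A constant difference in level between groups cancels in a within-mother change: at ICC 0.20 the simulated error of a nominal 5% test was 5.0% (groups of 8) and 4.7% (groups of 12). Only variation in the change matters. With ICC of the change and group size m, the SE should be multiplied by √(1 + (m − 1) × ICC).
- ICC 0.05: √1.35 = 1.16 (m = 8), √1.55 = 1.24 (m = 12).
- ICC 0.10: √1.70 = 1.30 (m = 8), √2.10 = 1.45 (m = 12).

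Over these values a nominal 5% test rejects about 9–17% of the time. Four group means leave 3 degrees of freedom, with a critical t of 3.18 against 2.01–2.04 when mothers are treated as independent. The variation between groups therefore cannot be estimated well here.

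**The case against.** The article never says that only mothers with three surveys are analysed. It names Stata, whose long-format ANOVA can keep incomplete mothers' available rows, and it does not exclude imputation. Missing-data rules are commonly left to a full protocol or analysis plan that is not shown. The analysis is secondary, exploratory and unpowered, and the strengths and limitations list disclaims generalisable quantitative claims for want of a control group. Location is among the sociodemographic variables, so differences between sites are not wholly ignored.

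Most of this stands, and it is why the point is conditional. It does not remove the point, because the method is named and not merely left open. In its usual form that method discards observed data, and the disclaimer about a control group does not address selection among the enrolled mothers. The disclaimer does weaken the group point, since it already gives up wider quantitative claims.

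A reader might infer more, and the documents do not support it:
- Gaps are not certain. They are likely, given foreseen drop-out and emailed surveys, but no rate is given.
- The bias need not flatter the intervention; the table shows both directions.
- Intervals of 5 and 4 weeks do not by themselves break sphericity.
- Nothing says that surveys stop when a woman leaves the classes.
- Nothing says that completion is by email only. The article says that participants are contacted by email, and help with completion is not ruled out, including for women who took in the study papers "either through reading or being read to".

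**Conclusion.** The point holds in conditional form. The standard version of the named ANOVA may discard a sizeable share of a sample of 32–48 and may bias the estimated change in either direction if loss depends on earlier scores. The sizes (20–50% of mothers, and roughly 0.3 to 1.1 EPDS points on a true fall of 4) rest wholly on assumed missingness, SD and correlations; under completely random loss the bias is nil. The consequence is limited because the analysis serves a secondary, exploratory aim, but the improvement is nearly free. On groups, the documents support only a caution about what the intervals cover. They do not show that the error bars are in fact too narrow.

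**What to change.** Replace the ANOVA with a linear mixed model fitted by REML to every available survey, with an unstructured covariance over the three waves and small-sample degrees of freedom. Report the mean changes from week 1 to 6 and from week 1 to 10 with 95% confidence intervals for each measure. State that the estimate relies on loss depending only on observed data and would remain biased if loss depends on unseen scores.

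Show the changes by singing group as well, and say that the intervals refer to these four groups. Adding group terms to the model would not make the result carry over to other groups.

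The cost is a few sentences in the analysis section and slightly more analysis work, with standard software.

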#### Qualitative

Framework method will be used to organise and analyse the qualitative data collected from intervention participants relating to implementation (ie, one-on-one interviews).^38^ The study teams across Denmark and Romania, with support from UCL, will develop a framework for use that is underpinned by approaches from implementation science, as previously outlined (eg, RE-AIM, Proctor *et al*’s taxonomy). The framework will be used to construct qualitative themes from the data that are relevant to our primary aim of evaluating implementation.

Drawing upon guidance from Braun *et al,*^39–41^ a reflexive thematic approach will be taken to analyse and evaluate experiences of the singing group and its perceived impact (ie, from the focus groups and journal entries). This will involve generating initial codes, searching for and reviewing themes, and then defining and naming themes. An inductive approach will be taken, working from the bottom-up, generating or drawing out knowledge from the data through examination of what is meaningful for the participants, thereby placing participant experiences at the heart of the analysis.^42^ This will allow us to evaluate perceived changes to mental health and well-being. Qualitative analysis software will be used to analyse and organise qualitative data.

Analyses will be undertaken by researchers in each country who were not part of the intervention development or any management processes. Project managers, researchers and members of the management team will also engage in regular biweekly meetings throughout data collection and analyses to engage in discussion about emerging findings as a form of reflexivity on our processes, thereby improving the rigour of the study.

## Ethics and dissemination

### Ethics

The National Ethics Committees in Romania (IRB-PH Protocol #2021-211217-012) and Denmark (case number 1-10-72-274-21) have approved the study, as has the Ethics Review Committee at the World Health Organization (ERC.0003714). All participants will need to provide informed consent in order to participate in the study. Consent forms for both countries are included as online supplemental files.

### Dissemination

The findings will initially be written up in a project implementation report, published by the WHO Regional Office for Europe and made publicly available. The aim of this report will be to share our processes and learning with commissioners, relevant organisations, policymakers and healthcare institutions so that it can be used in the future to provide guidance and best practice related to how arts and health interventions can be implemented in and scaled to different national and cultural contexts. Findings will also be published in peer-reviewed journals and shared at conferences, meetings and events, including webinars run by the WHO Regional Office for Europe.

### Data protection and confidentiality

In Denmark, all data will be stored and handled following the Danish law, specifically databeskyttelsesloven and databeskyttelsesforordningen. In Romania, data will be stored in line with local data management laws. In both countries, consent forms and identifiable data will be stored securely and only accessible by the project manager in each country. The quantitative data will be anonymised and the qualitative transcripts will be pseudonymised before being shared with researchers in each respective country for analysis. All identifiable data will be stored separately to participant demographics. Quantitative data will be collected using REDCap in Denmark and using Microsoft Teams in Romania. Any extracted data used for analysis will be stored on secure, password-protected storage systems that only the researchers doing the analysis and the project managers will have access to. Audio recordings from qualitative interviews will be deleted immediately from hand-held devices and from storage facilities as soon as transcripts have been created. All identiable information will be deleted at the end of the study. Anonymised and pseudonymised data will be stored in line with data collection policies in each country—5 years in Denmark and 5 years in Romania. Any adverse events or unintended consequences will be discussed at management meetings and documented by NF and CS at WHO/Europe in the track record document (see the Track record document section).
